### Outcome measures

For the first study objective, to determine the safety and feasibility of pairing VNS therapy with rehabilitation, we will report adverse events (AEs) in 3 categories: VNS surgery-related, VNS therapy-related, and VNS device related (*see the section* “*Expected risks*”). AEs will be labeled according to severity based on their impact on the patient. An AE will be termed *mild* if it does not have a major impact on the patient, *moderate* if it causes the patient some minor inconvenience, and *severe* if it causes a substantial disruption to the patient’s well-being. AEs will be categorized according to the likelihood that they are related to the study intervention. Specifically, they will be labeled *definitely unrelated*, *definitely related*, and *probably related* to the study intervention.

To determine feasibility, we will report treatment sessions attended by each participant and the number of dropouts in each group. The paired VNS intervention will be considered feasible if an adherence rate of at least 80% is achieved (≥15 of 18 sessions completed) and if the attrition (dropout) rate is no higher than 20% in each study group. We expect participants in both groups to participate in at least 50% of the assigned daily home exercises. We are also collecting data on patient satisfaction with the assigned intervention and adequacy of blinding procedures at the end of the study through a custom patient satisfaction questionnaire.

For the second study objective, to determine the potential efficacy of pairing VNS with rehabilitation, we will perform assessments of arm motor functions, activities of daily living, and quality of life. We will measure a change in Graded Redefined Assessment of Strength, Sensibility and Prehension (GRASSP) (41) performance from baseline to immediately after in-clinic therapy, 30-day and the 90-day timepoint. An increase of 4 points or greater in GRASSP score will be considered a clinically significant improvement (42). Secondary clinical outcome measures are the Toronto Rehab Institute Hand Function Test (TRI-HFT) (43), Capabilities of Upper Extremity Questionnaire (CUE-Q) (44), Spinal Cord Injury Independence Measure-III self-care subscore (45), and Spinal Cord Injury-Quality of Life (SCI-QoL) (46). All these measures are part of the National Institutes of Health common data elements for SCI. All measurements will be performed at baseline, at post-treatment (day 1), and at the 30-day and 90-day follow-ups. The core NINDS Spinal Cord Injury Common Data Elements—demographics, social status, general health history, history of the injury event, and neurological classification [International Standards for Neurological Classification of Spinal Cord Injury (ISNCSCI)]—will be completed within 30 days of collection of baseline data.

Other secondary outcome measures include assessing pain with the International SCI Pain Basic Data Subset (version 2) (47). Depression will be measured by use of the 8-item Patient Health Questionnaire (PHQ-8) (48, 49), with the item assessing for suicidality removed (49) (Table 1).

**Table 1 tab1:** Study timeline and procedures.

	Screening	Pre-implant baseline	Implant and randomization	Pre-therapy baseline	In-clinic therapy	Post-1 day	Post-30 day	Post-90 day
Eligibility criteria	X							
Informed consent	X							
Pre-surgical assessment	X	X		X		X	X	X
Prior and concomitant medications	X	X		X	X	X	X	X
Device implant			X					
Randomization			X					
VNS + rehabilitation					active VNS or control VNS	Home based active VNS or control VNS		
SCIM-III (SC)		X		X		X	X	X
GRASSP		X		X		X	X	X
TRI-HFT		X		X		X	X	X
CUE-Q		X		X		X	X	X
SCI-QoL		X		X		X	X	X
ISCIPBDS		X		X		X	X	X
PHQ-8		X		X		X	X	X
PSQ						X	X	X
Adverse events			X	X	X	X	X	X
Therapy compliance					X	X		

VNS, Vagus Nerve Stimulation; SCIMII-SC, Spinal Cord Injury Independence Measure III-Self-Care; GRASSP, Graded Redefined Assessment of Strength, Sensibility and Prehension; TRI-HFT, Toronto Rehabilitation Institute Hand Function Test; CUE-Q, Capabilities of Upper Extremity Questionnaire; SCI-QoL, Spinal Cord Injury Quality of Life; ISCIBDS, International SCI Pain Basic Data Subset (version 2); PHQ-8, Patient Health Questionnaire; PSQ, Patient satisfaction questionnaire.

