#### Safety monitoring plan

Participants will receive routine postsurgical care and follow-up after implantation. We will collect data on VNS surgery-related events (as detailed in the “Expected risks” section) and coordinate care with the surgeon for additional follow-up. We will monitor the participants’ vital signs during each therapy session (pre-and post-session) and as needed. We will also have a medical monitor consisting of 2 physicians with expertise in SCI at UTHealth Science Center at Houston who will review all AEs and significant AEs to determine the safety of continued participation of each participant in the study.

This study will be stopped prior to its completion if (1) the intervention is associated with adverse effects that call into question the safety of the intervention; (2) we experience difficulty in study recruitment or retention; (3) any new information becomes available during the trial that necessitates stopping the trial; or (4) other situations occur that might warrant stopping the trial. (5) Intolerance to individual sessions will be assessed on a case-by-case basis by the study investigators to determine the safety of continued participation in the study.

In the event of an IPG device malfunction, participants will be offered an evaluation by a neurosurgeon for removal or replacement of the device. If the participant prefers the device to be removed or replaced, they will be evaluated by a neurosurgeon.

At the end of the study, although the intention is to allow participants to keep the device so that long-term treatment is possible, some participants may prefer that the device be removed. If a participant discontinues the study or does not want further treatment, the generator and the portion of the lead coiled in the chest wound should be removed. The device is expected to last at least 5 years. If participants wish to continue therapy, the device is expected to be commercially available at that time for replacement surgery, and if a device is needed sooner during the study, one will be provided.

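### The adverse event severity grades overlap and are out of order, and the relatedness labels leave no place for an uncertain link

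*Protocol article*

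**What the plan says.** Safety belongs to the first study objective. Under Outcome measures the article says "we will report adverse events (AEs) in 3 categories": surgery-related, therapy-related and device-related. Two further classifications are then laid over these categories.

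- **Severity.** "AEs will be labeled according to severity based on their impact on the patient". The lowest grade, *mild*, is defined by the words "if it does not have a major impact on the patient". For the middle grade, *moderate*, the wording is "if it causes the patient some minor inconvenience". The highest grade, *severe*, refers to well-being and applies "if it causes a substantial disruption to the patient" in that respect.
- **Relatedness.** "AEs will be categorized according to the likelihood that they are related to the study intervention". Three labels follow, introduced as the specific ones to be used: *definitely unrelated*, *definitely related* and *probably related*.

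Expected risks, Adverse event reporting and Safety monitoring plan give no other definition of severity or causality. The split between serious and non-serious events under Adverse event reporting only sets how long events are collected. The medical monitor is made up of two physicians, "who will review all AEs and significant AEs to determine the safety of continued participation of each participant in the study".

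**The concern.** A severity scale should give each event one grade, and a worse event should never get a lower grade than a lesser one. A relatedness scale said to rest on likelihood should have somewhere to put an event whose cause is in doubt. As worded, neither scale does this.

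The analysis is mostly descriptive (Sample size, data collection and analysis), so the tabulated labels are reported as they stand, with no formal test behind them. If two careful graders can give the same event different labels, part of the difference between the arms in those tables may reflect the grader and not the treatment. The article also says that the pilot is meant to refine the protocol for a larger trial, so scales left uncorrected could be carried forward into it.

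**Working it through.** No sample size, power or error rate depends on this point, and the plan gives no figure to reproduce. The check is one of logic on the stated wording.

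**Severity.** Take four levels of impact in increasing order and test each against the three definitions. The table assumes that a major impact and a substantial disruption begin at about the same point.

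| Impact of the event | Meets *mild* (no major impact)? | Meets *moderate* (some minor inconvenience)? | Meets *severe* (substantial disruption)? | Grade available |
|---|---|---|---|---|
| A. No inconvenience | yes | no | no | mild |
| B. Minor inconvenience | yes | yes | no | mild or moderate |
| C. More than minor, less than substantial | yes | no | no | mild |
| D. Substantial disruption | no | no | yes | severe |

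1. Row B: a minor inconvenience is by meaning not a major impact. Everything that meets *moderate* therefore also meets *mild*, and the grades are not mutually exclusive.
2. Row C: the event is worse than B, yet only *mild* can take it. If B is graded *moderate*, the worse event gets the lower grade, so the scale is out of order.
3. An unstated convention of assigning the highest grade met would settle row B as *moderate*. Row C would still be *mild*, so the misordering remains.

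**Relatedness.** Set the labels along the likelihood they are said to express.

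| Judged link to the intervention | Label available |
|---|---|
| Certainly none | definitely unrelated |
| Unlikely, or possible | none |
| Probable | probably related |
| Certain | definitely related |

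Let *d* be the number of events that are clearly probable or definite, and *u* the number whose link is uncertain. If all uncertain events are pushed down, the related count is *d*. If all are pushed up, it is *d* + *u*. The reported count can therefore differ by (*d* + *u*) − *d* = *u* through labelling alone. A literal grader, who reserves *definitely unrelated* for certainty, moves towards *d* + *u*; a grader reluctant to call a doubtful link probable moves towards *d*. The article gives no adverse event frequencies, so *u* cannot be filled in.

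**Are uncertain events foreseeable?** Three places in the article bear on this.

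- Expected risks lists autonomic dysreflexia, worsening spasticity and pain at the stimulation site as therapy-related, and lists pain among the surgery-related risks too.
- The Introduction describes dysreflexia as a known complication in cervical injury and counts pain among the known complications of spinal cord injury.
- The Introduction also states that there are no human trial data in this population.

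The same event can therefore plausibly come from the injury, the operation or the stimulation, with little prior experience to separate them.

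**The case against.** The strongest case on the other side is that little depends on these labels. The Abstract says that safety is assessed by the occurrence of adverse events in each group, and occurrence does not change with the grade. The feasibility criteria use attendance and dropout only. The stopping criteria in the Safety monitoring plan contain no grade threshold, and the medical monitor sees all events whatever their label. All of this stands, and it limits the harm to the severity and relatedness tables.

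Some stronger readings are tempting but unsupported:

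- A reader might infer that the adverse event counts by arm cannot be interpreted at all. Overall occurrence by arm is unaffected; only the breakdown by grade and relatedness is.
- A reader might infer that some events have no severity grade. On the reading used in the table above, the open-ended *mild* definition takes them. Events without a grade would arise only if a major impact started below a substantial disruption, which the article does not say.
- A reader might offer dysphagia as an event confounded with the injury. Ongoing dysphagia or swallowing difficulty is excluded at entry (Study population), so a pre-existing problem cannot be the source of confusion.
- A reader might note that one participant in an arm of four is 1/4 = 25 percentage points. That holds for any yes/no outcome at this sample size and does not measure this defect.

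Vital signs and pain score are taken before and after each therapy session, and dysreflexia and worsening spasticity are recorded (Expected risks). This helps with the timing of events around a session. It does not supply a label when the judgement remains uncertain.

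It can also be said that a journal article condenses a fuller protocol. That would excuse an omission. Here both scales are written out, and the fault lies in what is written.

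**Conclusion.** The point holds, at moderate weight. The severity definitions are neither mutually exclusive nor properly ordered, and the relatedness labels have no place for an uncertain link. The severity and relatedness tables for a first-objective outcome are therefore open to avoidable misclassification. Overall adverse event occurrence by arm, the medical monitor's review and the feasibility criteria are untouched.

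The size cannot be given as a number. For relatedness it equals the number of uncertain events; for severity it is the number of events that fall in rows B and C. Neither is documented, and the article does not say that minor events will be the majority.

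The conclusion rests on two assumptions: that the definitions are applied as worded, and that no further grading convention exists beyond what the article states. A convention of taking the highest grade met would remove the overlap but not the misordering or the relatedness gap.

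**What to change.** 1. Replace the severity wording with ordered, mutually exclusive grades. One option is degree of interference with usual activities: noticed without interference, some interference, usual activities prevented. State that each event receives one grade.
2. Add at least one relatedness label between *definitely unrelated* and *probably related*, such as *possibly related*. State before unblinding whether events with that label count as related in the tables. The exact number of levels is a matter of choice; one intermediate label closes the hole.
3. Apply the revised scales to any events already recorded. Trial status reports four participants implanted and does not say whether events have occurred. A person masked to arm should do this. The research coordinator shares responsibility for collecting adverse events but may also set the device parameters by allocation, and should not do the re-grading.

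The cost is minor: revised wording in the protocol and case report form, and re-grading of whatever events exist. If possible links are counted as related, the related-event count may rise slightly, and the report should say so.

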### Patient and public involvement

Patients and/or the public were not involved in the design of this protocol. However, we will invite the participants of this study to provide input on study procedures, such as the feasibility of attending in-clinic sessions three times per week and 30-min home exercise program, the relevance of the tasks included in the protocol to their daily life, the burden of data collection, adequacy of blinding procedures and their experiences with the study participation. This information will be considered to refine this protocol further for a larger RCT.

### Sample size, data collection and analysis

We plan to enroll 8 participants and randomize them 1:1 to the active VNS or sham VNS group to study the safety and feasibility and to inform the design of a larger trial. No sample size calculations were performed to study the potential efficacy. We base this sample size on budgetary considerations during funding period.

Case report forms will be the primary method of obtaining data. Data will then be directly entered into the electronic database. Prior to the start of the study, the investigator will complete a Delegation of Authority Form showing the signatures and handwritten initials of all individuals authorized to perform study tasks, specifically those authorized to make or change entries on case report forms. The investigator or designee will provide completed case report forms for each participant. All required data are to be recorded in the electronic database promptly. The electronic data will be stored on a secured server and will be backed up daily to mitigate the risk for data loss. The investigators (RK and NY) will be solely responsible for the accuracy of the data.

Most of the planned analyses are descriptive owing to the pilot nature of the proposed study. Continuous variables will be summarized by mean, SD, or median quartiles as appropriate and categorical variables will be summarized via frequency and percentages. Outcome variables will be summarized separately for each randomization arm in graphs or tables, following the intention-to-treat principle.

## Ethics and dissemination

### Informed consent

Informed consent will be obtained from eligible participants by the PI and/or the research coordinator, and potential participants will be given sufficient time to decide to participate. The research coordinator will be involved in the consent process if there is a conflict of interest between potential research participants and the clinician PI. All procedures will be fully disclosed to the participants, and we will give them as much information as possible about the intervention and the data analysis. The participants will be given the opportunity to ask questions. They will be reassured that their participation in this study is voluntary and that they have the right to withdraw from the study at any time. Any new findings developed during this research that may affect the participants’ willingness to continue will be provided to them. The participants will be asked to sign a Research Subject Authorization Confidentiality and Privacy Rights form to comply with HIPAA regulations. This protocol and the associated informed consent documents have been approved by the Committee for the Protection of Human Subjects (CPHS) at McGovern Medical School in the UTHealth Science Center at Houston (#HSC-MS-22-0579).

### Confidentiality of patient data

All patient records will remain confidential. Data with Protected Health Information (PHI) will be de-identified and given a participant ID found on the Linking Log. The Linking Log is a separate file in a separate folder located on the PI’s desktop computer.

All research staff must have the Collaborative Institutional Training Initiative (CITI) training, which covers information privacy and security training to minimize the risk for privacy breaches. Efforts to maintain the confidentiality of all participants are per standards set forth by the CPHS at McGovern Medical School in the UTHealth Science Center at Houston.

### Expected risks

VNS surgery-related risks will include postsurgical complications including but not limited to dysphagia, hematoma, hoarseness of voice, vocal cord paralysis, facial paralysis, Horner syndrome, bradycardia, oedema, pain, and postsurgical infection (50, 51). We expect <1% surgery-related unresolved AEs at the 90-day follow-up on the basis of the results of the clinical trial in stroke. Risks related to almost any surgery include but are not limited to anesthesia-related adverse effects, pain, blood clots, infection, and bleeding.

VNS therapy-related risks include changes in blood pressure, heart rate, and respiratory rate, autonomic dysreflexia, worsening spasticity, and pain at the stimulation site. We will monitor blood pressure, heart rate, pain score, and respiratory rate before and after each therapy session and as needed if the patient reports any symptoms of discomfort, dizziness, etc. We will also record any incidence of autonomic dysreflexia, worsening spasticity symptoms, and development of any abnormal sensation. Other possible VNS-related symptoms include dyspepsia, dysphagia, hoarseness, hiccups, cough, laryngospasm, nausea, pain, paraesthesia, and pharyngitis.

VNS device-related events are rare (fewer than 1 in 100 cases). The lead or stimulator could move or protrude from the skin. Other risks include the risk that confidentiality could be inadvertently compromised.

### Adverse event reporting

The investigators and/or research coordinator will be responsible for collecting and reporting AEs during the trial. Participants will be recommended and encouraged to report any unanticipated problems or AEs throughout the course of the study (from the time of consent to the completion of the study) to the research coordinator by email or phone. The research coordinator will communicate all unanticipated problems and AEs to the PIs, who will record all reportable events with start dates occurring any time after informed consent is obtained until 7 days (for non-serious AEs) or 6 weeks (for serious AEs) after the completion of the intervention. Records of unanticipated problems and AEs will include the date, the details of the problem/event, and when and how the problem/event was reported to the investigators. The PI will report problems according to the UTHSC-Houston IRB policy.

#### Safety monitoring plan

Participants will receive routine postsurgical care and follow-up after implantation. We will collect data on VNS surgery-related events (as detailed in the “Expected risks” section) and coordinate care with the surgeon for additional follow-up. We will monitor the participants’ vital signs during each therapy session (pre-and post-session) and as needed. We will also have a medical monitor consisting of 2 physicians with expertise in SCI at UTHealth Science Center at Houston who will review all AEs and significant AEs to determine the safety of continued participation of each participant in the study.

This study will be stopped prior to its completion if (1) the intervention is associated with adverse effects that call into question the safety of the intervention; (2) we experience difficulty in study recruitment or retention; (3) any new information becomes available during the trial that necessitates stopping the trial; or (4) other situations occur that might warrant stopping the trial. (5) Intolerance to individual sessions will be assessed on a case-by-case basis by the study investigators to determine the safety of continued participation in the study.

In the event of an IPG device malfunction, participants will be offered an evaluation by a neurosurgeon for removal or replacement of the device. If the participant prefers the device to be removed or replaced, they will be evaluated by a neurosurgeon.

At the end of the study, although the intention is to allow participants to keep the device so that long-term treatment is possible, some participants may prefer that the device be removed. If a participant discontinues the study or does not want further treatment, the generator and the portion of the lead coiled in the chest wound should be removed. The device is expected to last at least 5 years. If participants wish to continue therapy, the device is expected to be commercially available at that time for replacement surgery, and if a device is needed sooner during the study, one will be provided.

